#### Dutch RCT

Women are asked to return all pills they have not used to the pharmacy every time they collect a new set of pills, in order to check compliance with FA supplementation.

All analyses will be performed according to the intention-to-treat principle. In addition, alternative per protocol analyses will be performed, excluding all participants who were not compliant with FA supplementation. For the analysis on the effect of FA supplementation on CMs, groups 1 and 2 (low dose) and 3 and 4 (high dose) will be combined, since no interaction between early FA and late FA supplementation is expected.

### Outcome measures

#### Italian RCT

The primary study outcome is the total number of adverse pregnancy outcomes as listed above.

#### Dutch RCT

The primary outcomes include all FA-related CMs.

Preterm birth is defined as a gestational age <37 weeks.

Pre-eclampsia is defined as a systolic blood pressure ≥ 140 mmHg and/or diastolic blood pressure ≥ 90 mmHg after 20 weeks of gestation among women with previously normal blood pressure, combined with proteinuria (≥300 mg/24 hours).

### Sample size

In the original protocols, sample size was computed considering CMs as end point. However, given the increasing interest toward the effect of FA supplementation on all pregnancy outcomes on the one hand, and the difficulties encountered in subjects recruitment on the other hand, we foresee to analyze the data considering all the adverse outcomes of pregnancy taken together in a global end point (e.g.: CMs, miscarriage, pre-eclampsia, preterm birth, small for gestational age, abruptio placentae).

Since the frequency of the cumulative group of adverse pregnancy outcomes has an estimated frequency of 30% (unpublished observation), a total of about 1,000 pregnancies need to be evaluated to detect an absolute reduction of the frequency of 8% with allocation ratio 1:1, alpha error of 0.05, power of 80%.

After one year of pregnancy planning or active pregnancy search, a pregnancy rate of 80-85% is expected. Since the sample size needed to analyze outcomes separately is large, this project also promotes an international prospective meta-analysis.

### Data analysis

The analysis will be conducted by protocol and by intention to treat. A multivariate model will be used where unbalanced characteristics will be considered. A subgroup analysis will be performed for women with assisted reproduction.

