### Randomization procedures

#### Italian RCT

After giving informed consent, women are randomly assigned to receive a pill containing 4 mg of FA (treatment in study) or 0.4 mg of FA (referent treatment) daily. The randomization code is generated by a web-based patient randomization system, stratified according to the enrolment site and the maternal age group. The study is double-blinded: subjects, investigators and research staff are blinded to the randomization assignments.

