#### Dutch RCT

After giving informed consent, women are randomized to one of the four groups. Randomization is not stratified. Every four participants per research centre are assigned to a different study group, resulting in equal distributions among the study groups. The study is double-blinded: subjects, investigators and research staff are blinded to the randomization assignments.

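### Covariates are chosen by observed imbalance, so the adjusted model depends on chance and would ordinarily omit the factors that the randomization balances

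*Protocol article*

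**What the plan says.** The Data analysis section of the protocol article has three sentences and serves both trials. Its only rule on adjustment is "A multivariate model will be used where unbalanced characteristics will be considered". It lists no covariates, gives no test or threshold for imbalance, and does not say whether the adjusted or the unadjusted result is the main one. The sentence before it reads "The analysis will be conducted by protocol and by intention to treat", without ranking the two.

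Under Randomization procedures, Italian allocation is "stratified according to the enrolment site and the maternal age group". For the Dutch trial the same section states "Randomization is not stratified" and then "Every four participants per research centre are assigned to a different study group". Nothing in the article says that site, centre or maternal age group will be in the model, and nothing excludes them.

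**The concern.** In a properly randomized trial, baseline differences between arms arise by chance. Whether a characteristic happens to differ says nothing about whether it predicts outcome. Covariates are better chosen in advance, for their prognostic value and their role in the design.

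A rule based on imbalance does the reverse in two ways. It brings in whatever differs by accident, so the model is unknown until the data are seen, and with no criterion stated the choice is left to the analyst. It also tends to leave out the variables used in allocation, because allocation has made them similar between arms. If those variables predict outcome and the analysis ignores them, the standard error is too large for the design and some power is lost. The Recruitment section lists Italian randomization centres that run from assisted reproduction centres to general practitioners, and the analysis section plans an assisted-reproduction subgroup. Differences in risk between sites are therefore plausible, though the article does not quantify them.

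**Working it through.** **1. The plan's own figure.** Inputs from the Sample size section: 30% versus 22% (an absolute reduction of 8 points), 1:1 allocation, alpha 0.05, power 80%. With a mean risk of 0.26, two-sided:

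n per arm = [1.96·√(2·0.26·0.74) + 0.8416·√(0.30·0.70 + 0.22·0.78)]² / 0.08² = 470.7, so 471 (942 in total).

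With continuity correction: (470.7/4)·[1 + √(1 + 4/(470.7·0.08))]² = 495.4, so 496 (992 in total). This reproduces the stated total of about 1,000. At 500 per arm, power without the correction is 82.3%. The point here does not change that number.

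**2. What chance selection does.** Assume that imbalance means p<0.05 and that the candidate covariates are independent. The chance that at least one is selected is 1 − 0.95^5 = 22.6% for five candidates and 1 − 0.95^10 = 40.1% for ten. Simulation with five candidates gave 22 to 24%.

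**3. Whether the rule would pick up the allocation factors.** Simulated trials used 1,000 pregnancies, 10 sites, 2 age groups and blocks of four within site by age. Neither site nor age met p<0.05 in any run.

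That simulation treats all randomized women as analysed, whereas the Sample size section expects 80–85% to conceive. If conception is unrelated to arm and age is exactly balanced at randomization, keeping a fraction q of women leaves a variance for the between-arm difference of (1 − q) times that under simple randomization. The standardized difference then has SD √(1 − q): √0.20 = 0.45 or √0.15 = 0.39. The threshold of 1.96 lies 1.96/0.45 = 4.4 or 1.96/0.39 = 5.0 of these SDs away, so crossing it would be very rare.

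**4. Effect on the test.** Same simulation, 3,000 runs per cell, treatment log odds ratio −0.42 (about 30% to 22%). The SD is that of the combined site and age effect on the log-odds scale. It is an assumption, shown over a range.

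| SD of site and age effect | Type I error, imbalance rule | Type I error, site and age in model | Power, imbalance rule | Power, site and age in model |
|---|---|---|---|---|
| 0 | 4.7% | 4.9% | 81.5% | 81.9% |
| 0.3 | 5.1% | 5.7% | 80.6% | 81.4% |
| 0.6 | 4.2% | 4.9% | 78.5% | 80.3% |
| 1.0 | 3.2% | 4.9% | 72.4% | 78.5% |

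Monte Carlo error is about 0.4 points for type I error and 0.7 points for power. The relevant comparison is within a row: 0.4, 0.8, 1.8 and 6.1 points of power. The first two are within simulation noise.

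**5. A second simulation.** This one had 15 sites by 3 age groups and 4,000 runs, and compared an unadjusted test with Mantel–Haenszel. Power was 81.3 versus 81.9%, 78.9 versus 80.8% and 73.2 versus 77.8% for weak, moderate and strong strata: gains of 0.6, 1.9 and 4.6 points. It did not apply the plan's imbalance rule. In the simulation of step 4, however, the unadjusted test and the imbalance rule gave nearly the same power (81.6 and 81.5% at SD 0; 72.4% for both at SD 1.0).

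**The case against.** The strongest reply is that the article says only that unbalanced characteristics will be considered. It does not say that nothing else enters the model, and a full covariate list is commonly left to the analysis plan, which is not shown. This stands in part. A reader might infer that the plan never adjusts for site or age, but the text does not support that: their omission follows from applying the stated rule, not from any exclusion. What remains is that the article is not silent. It states a principle of selection, and an analysis plan that followed it would inherit the weakness.

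Second, stratification balances the women randomized, whereas the endpoint is assessed in those who conceive, and the per-protocol set also drops non-compliant women. Balance there is approximate, and with no criterion stated an analyst could call either factor unbalanced. That is right, and it is why the claim is limited to what would ordinarily happen. The calculation for conception above suggests that it would be rare at p<0.05, but it assumes conception unrelated to arm and does not cover exclusions for non-compliance.

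Third, the numbers of sites and age groups and their prognostic strength are assumed. That also stands: a loss of 5 to 6 points needs strong effects that the article does not document.

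Fourth, the Dutch statement that randomization is not stratified can fairly be read as meaning no stratification on participants' characteristics, since the next sentence makes the sets of four per centre clear. A reader might call this a contradiction, but it is largely terminology. Age is not a Dutch stratification factor.

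**Conclusion.** The point holds as a weakness in a stated rule that costs almost nothing to remedy. Selecting covariates by observed imbalance makes the adjusted model depend on chance, and would ordinarily omit site and maternal age group in the Italian trial and centre in the Dutch trial.

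A reader might infer that leaving these factors out produces false positives. It does not: simulated type I error under the rule was 3.2 to 5.1%, at or below nominal within simulation error. The cost is a somewhat conservative test and about 0 to 6 points of power, under 1 point if the factors are weakly prognostic. The upper end rests on assumed site and age effects and should not be read as the expected loss. Even so, the Sample size section targets only 80% power and the Objectives section reports that recruitment is behind plan, so there is little power to spare.

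The other cost is that the adjusted result stays open to choice among models. The frequency of chance selection (about 23% with five candidates) depends on the assumed p<0.05 criterion. How far the treatment estimate could move through analyst choice was not quantified.

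**What to change.** Replace the sentence on the multivariate model with a prespecified one, along these lines: the adjusted comparison in the Italian trial includes enrolment site (or a grouping of sites fixed in advance) and maternal age group; in the Dutch trial it includes research centre; if the two trials are pooled, a term for trial is added; adjustment for characteristics found to differ at baseline is confined to sensitivity analyses.

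Any grouping of small sites needs its rule written down before unblinding, or the same discretion returns. The article does not spell out a pooled model, so the trial term is conditional, and nothing here requires a term for the later Dutch dose groups. It would help to add that Dutch allocation is balanced in sets of four within centre, but that is a clarification only.

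The cost is wording. Site and centre are already used in allocation, maternal age group is an Italian stratification factor, and the sample size is unchanged.

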### Ethical considerations

#### Italian RCT

The project has been approved by the ethical committee of the randomization centres, and all subjects provide written informed consent.

#### Dutch RCT

The project has been approved by the ethical committee of the VU University Medical Center, and all subjects provide written informed consent.

### Data Safety Monitoring Committee

#### Italian and Dutch RCT

The study will be interrupted if:

• there is evidence that the study drug causes suspected unexpected serious adverse reactions (SUSAR) or serious adverse events (SAE) in the short or long term;

• the frequency of any reproductive adverse event or pregnancy complication in the overall group of women in the study is higher than the expected frequency.

To regularly check this, the Data Safety Monitoring Board (DSMB) will evaluate the global frequency of reproductive adverse events or pregnancy complications in the total sample of randomized women, and will communicate it to the General Coordination Centre (GCC).

### Relevance for society

Between 200,000 and 300,000 cases of NTDs are born each year worldwide. Other CMs that might be prevented with FA supplementation are heart anomalies, limb defects, urinary tract malformations, oral clefts and Down syndrome. These anomalies far outnumber the figures for NTDs. It must be stressed that the potential impact on child health is huge. Even a 13% reduction of all CMs means 39,000 healthy infants per year out of 10 million births in the WHO European Region. The most common and severe CMs are included among a selected group that may be more sensitive to the preventive action of FA (NTDs, oral clefts, cardiac defects, urinary tract anomalies, limb reduction defects, omphalocele, anal atresia). Even an apparently small decrease (e.g.: 20-30%) of the frequency of all CMs through a primary prevention intervention is an extremely important public health issue, since we can secure the health of a great number of children that would otherwise be affected as well as save money.

All these CMs have a huge impact on the health, quality of life, and life expectancy of the children. They also have a major impact on the lives and quality of life of their family. If the preventive effect of FA for CMs other than NTDs were to be proven, this fact could be used to further conduce the pre-conceptional use of FA supplements through patient education strategies, thereby increasing the overall effect of FA prevention. If higher doses of FA supplementation appear to be more effective than the now recommended daily dose of 0.4 mg, this would be an improvement of an existing intervention with huge impact.

But it is not only CMs that might be affected by FA supplementation. The risk of pre-eclampsia and preterm birth is also likely to be reduced by FA supplementation. The prevention of both CMs and preterm birth will result in a reduced perinatal death rate.

The proof of additional preventive effects of FA over the currently accepted effects of 0.4 mg on NTDs only has a significant impact on the need for, and the possibilities to reduce, social inequalities in health.

## Discussion

In conclusion, the total group of adverse pregnancy outcomes is the single major cause of infant morbidity, mortality and disability in all countries. Therefore even an apparently small decrease (e.g.: 20-30%) of the frequency of major adverse pregnancy outcomes through a primary prevention intervention is an extremely important public health issue, since we can secure the health of a great number of children who would otherwise affected. Prevention in this field is therefore highly important.

We designed an RCT to assess the effect of FA peri-conceptional supplementation of 4 mg/day compared to the 0.4 mg/day standard dose on reducing the occurrence of major adverse pregnancy outcomes. The project will also give the opportunity to promote fully standardized pre-conceptional counselling in all the women contacted to participate and then to promote a wider prevention of adverse pregnancy outcomes and maternal-infant health.

## Abbreviations

BMI: Body mass index; CI: Confidence interval; CMs: Congenital malformations; CP: Community pharmacy; DSMB: Data safety monitoring board; EUROCAT: European surveillance of congenital anomalies; FA: Folic acid; GCC: General Coordination Centre; HCP: Health care provider; IVF: In vitro fertilisation; MD: Mean difference; MRC: Medical Research Council; NTDs: Neural tube defects; OR: Odds ratio; RBC: Red blood cell; RCT: Randomized clinical trial; RR: Relative risk; SAE: Serious adverse event; SUSAR: Suspected unexpected serious adverse reaction.
